## 4. Discussion

Secondary hydrocephalus is a well-known complication of sABIs that may delay or negatively affect patients’ recovery, apparently resulting from multiple factors. Currently, there is no gold standard for its detection, but early diagnosis and treatment are fundamental to improve patients’ prognosis and rehabilitation outcomes [20,44]. In this paper, we have described the study protocol of a prospective cohort study that aims at validating a new clinical protocol for the diagnosis of secondary hydrocephalus. 

The liquor subtraction test is essential for the diagnosis [5,8,45]; however, because of its transient effect, a standardized and timely evaluation is mandatory.

Secondary hydrocephalus is under-diagnosed and less studied compared to idiopathic normal-pressure hydrocephalus (iNPH). In a recent retrospective study, Lalou et al. [44] found that resistance to CSF outflow and the pulse amplitude of intracranial pressure were significantly lower in PTH compared to iNPH and did not always reflect the degree of hydrocephalus or atrophy reported on CT/MRI. More studies on CSF dynamics are needed in order to assess the CSF circulation between people with trauma or hemorrhage compared with people with iNPH. 

Wu and colleagues [46] described secondary low-pressure hydrocephalus (LPH) and negative-pressure hydrocephalus (NegPH) that have been rarely reported and insufficiently recognized pathophysiologically. They suggested that, although the current classifications of hydrocephalus fail to provide clinical guidance to manage LPH and NegPH properly, they offer a new therapeutic viewpoint in order to recover the ventricular enlargement back to a normal size as far as possible from hydrocephalus with ventriculomegaly, regardless of the ventricular pressure. 

Given these premises, we plan to systematically submit all patients with sABIs to a timely and structured protocol that includes a clinical assessment, tap test, CSF examination, and neurophysiological and neuroradiological exams. In our protocol, neuroimaging is performed according to the timing based on the literature and our experience, in order to capture the hydrocephalus as soon as possible. 

Some patients with sABIs present with prolonged disorders of consciousness (unresponsive wakefulness syndrome or minimal conscious state). Arnts and colleagues [19] discussed both the difficulties in the diagnosis and the dilemmas in the treatment of CSF disorders in patients with prolonged disorders of consciousness and reviewed evidence from the literature to implement an active surveillance protocol for the detection of this late but treatable complication. Moreover, they advocated a low threshold for cerebrospinal fluid diversion when hydrocephalus is suspected, even months or years after brain injury. In addition, an accurate and structured diagnostic investigation with CT and MRI allows the identification of patients clinically not suspected of hydrocephalus. 

It is generally recognized that a multidisciplinary approach plays an important role in the management and treatment of suspected hydrocephalus cases, because risks and benefits should be carefully considered and calibrated on the patient [1,7]. In our protocol, the multidisciplinary team represents the most important feature since the exchange of views among experts allows for evaluating patients’ conditions in deeper detail and identifying the best care pathway.

This new clinical diagnostic protocol has been designed to integrate all the aforementioned ingredients. 

One important limitation is that the new protocol has already been adopted by our institution; thus, carrying out a randomized clinical trial to assess its efficacy is not feasible for ethical reasons. The second limitation is that the historical cohort may not include complete information on the variables of interest. 

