## Abstract

Background: Secondary hydrocephalus is a well-known complication of severe acquired brain injuries (sABIs) often diagnosed during inpatient rehabilitation. Currently, there is no gold standard for its detection. Therefore, we designed a novel clinical diagnostic protocol that integrates clinical, functional, biochemical and neuroradiological assessments to improve the accuracy of its diagnosis in patients with sABIs. Methods: This prospective cohort study will be conducted in a tertiary referral rehabilitation center in Italy. A historical cohort of patients will be compared with a prospective cohort undergoing the new clinical diagnostic protocol. Expected Results: The expected results include an increase in the proportion of diagnosed cases, a reduced incidence of clinical complications, an increase in the rehabilitative outcomes at discharge, a significant reduction in the length of hospital stay, and useful information about the diagnostic and prognostic value of the neuroradiological characteristics. Conclusion: We expect that this clinical diagnostic protocol will result in a more appropriate assessment and timely treatment of secondary hydrocephalus in patients with sABIs, with the ultimate goal of improving their prognosis. In addition, it could be adopted by other rehabilitation centers to improve hydrocephalus diagnosis and treatment, thereby reducing the length of hospital stay and accelerating recovery with benefits for both patients and hospitals.

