In a previous study, a 13.2% incidence of secondary hydrocephalus was reported among 621 hospitalized patients with sABIs [7]. The diagnosis was based on the previously indicated combination of clinical and radiological criteria, but we hypothesized that cases may have been under-detected, especially in patients with disorders of consciousness and/or many confounding comorbidities, due to the absence of a reference standard. In addition, the study showed that after VPS placement, most patients had a clinical improvement and none worsened; however, a delay in surgical treatment resulted in a longer hospitalization and was associated with worse outcomes. That study underscored the need for a more standardized approach to the diagnosis of secondary hydrocephalus, with a better timing in the evaluation of patients with sABIs during inpatient rehabilitation in order to improve the selection of those who may benefit most from surgical treatment [17].

In this position paper, we describe a diagnostic protocol for hydrocephalus that integrates clinical, functional, biochemical and neuroradiological assessments. The aims of the protocol are as follows:To increase the hydrocephalus detection rate;To reduce the time for hydrocephalus diagnosis/surgical treatment;To improve the clinical rehabilitative outcomes at discharge;To reduce the overall length of hospitalization (LOS) and the occurrence of complications in patients diagnosed with and treated for hydrocephalus.

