Diagnosis confirmation derives mainly from the improvement of the patient’s clinical/neurological condition after CSF TT, measured as an improvement in the score of the clinical scales before and after the test or as an improvement in the performances in the functional tests. The main clinical rating scale is the Disability Rating Scale (DRS). The Levels of Cognitive Functioning (LCF) scale corroborates the DRS result. The Coma Recovery Scale Revised (CRS-R) will be used for patients with low responsiveness or severe disturbance of consciousness. 

Specifically, the diagnosis will be confirmed when at least one of the following changes occurs after TT:
Decrease in the DRS score;Increase in the LCF score;Increase in one of the CRS-R scale’s items that identify a minimally conscious state or emergence from a minimally conscious state;Improvement in one of the functional tests (TUG, 10 mWT, POMA).

Patients with a confirmed diagnosis will receive an indication of surgical treatment with shunt placement.

Both the severity of the clinical condition and the consent being denied by family are reasons that preclude the intervention, even in the case of a diagnosis confirmation.

During the hospital stay, the multidisciplinary team will evaluate the presence of suspected hydrocephalus in patients with no previous diagnosis. Patients with suspected hydrocephalus will be treated following the clinical diagnostic protocol just described.

The study flow is described in Figure 2. 

All patients will undergo a reassessment of all clinical and functional scales, neurological and neurophysiological examinations and a brain CT scan at three time points: 1 month after surgery for those treated with a VPS/VAS or at 3 months from hospital admission for patients without a diagnosis of hydrocephalus or who did not receive a VPS/VAS placement (T2); at discharge (T3); and 1 year after hospitalization (T4). All the patients will undergo a brain MRI at T3 and, if prescribed by the multidisciplinary team, at T4. 

Table 1 summarizes the clinical parameters, clinical measurement scales, functional tests, and neurophysiological and neuroradiological exams included in the study.

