### 2.5. Statistical Analysis Plan

Continuous variables will be presented as the mean and standard deviation or as the median and interquartile range. Normality in the distribution will be tested with the Shapiro–Wilk test. Categorical variables will be summarized in terms of absolute and relative frequencies.

To determine whether the new diagnostic protocol can improve the ability to detect hydrocephalus as well as the timeliness of the diagnosis and the clinical rehabilitative outcomes, the historical and prospective cohorts will be compared with respect to the following: hydrocephalus diagnosis detection rate, time from admission to diagnosis, LOS, incidence of clinical complications, and DRS and LCF scores at discharge (T3). In the subgroup of patients with low responsiveness, the clinical rehabilitative outcome at discharge will be measured using the CRS-R score. Continuous variables will be compared using Student’s *t* test, when normally distributed, or the Mann–Whitney U test otherwise. Categorical variables will be compared using Pearson’s χ^2^ test or Fisher’s exact test as appropriate. The same tests will be used to compare patients with and patients without a diagnosis of hydrocephalus belonging to the prospective cohort, in terms of the following: clinical rehabilitative outcome at T3 and T4 measured using the DRS, LCF and CRS-R scale scores; evolution from T0 to T4 of quality of life measured using the QOLIBRI-OS; neuroradiological characteristics at T1 and T3 or T4 measured using Evan’s index, callosal angle and volumetric analysis. To complement the information provided by the statistical tests, differences between groups will be quantified in terms of the effect size (standardized mean differences for continuous variables; difference between proportions or odds ratios for categorical variables) and its standard error. In addition, outcome variables will be compared between the historical and prospective cohorts, adjusting for demographic and clinical confounders in multivariable regression analyses. Confounders to be included in the models are those significantly associated with the outcomes and significantly different between the two cohorts. 

Two-sided tests will be carried out, and the statistical significance level will be set at 0.05. All analyses will be performed with Stata version 17.0 (Stata Corp., College Station, TX, USA).

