## 5. Conclusions

We designed a novel clinical diagnostic protocol to improve the accuracy of secondary hydrocephalus diagnosis in patients with sABIs. We expect that it will result in a more appropriate assessment and timely treatment of patients, with the ultimate goal of improving their prognosis.

Should this clinical diagnostic protocol prove to be useful, it could be adopted by other rehabilitation centers to improve hydrocephalus diagnosis and treatment, thereby reducing the length of hospital stay and accelerating recovery with benefits for both patients and hospitals. 

In addition, this protocol may inform future diagnostic and prognostic guidelines for the inclusion of the tap test, timely and standardized neuroimaging and an early approach of the multidisciplinary team in the standard of secondary hydrocephalus diagnosis in patients with sABIs. 

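### Validation and better accuracy are claimed, but the diagnosis itself is judged only by detection rate and time to diagnosis, which cannot separate better detection from over-diagnosis

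*Protocol article*

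**What the plan says.** **Purpose.** Section 4 (Discussion) says that the study "aims at validating a new clinical protocol for the diagnosis of secondary hydrocephalus". The Abstract gives the purpose of the protocol as "to improve the accuracy of its diagnosis in patients with sABIs", and section 5 (Conclusions) repeats "to improve the accuracy of secondary hydrocephalus diagnosis in patients with sABIs". The formal list of aims in section 1 is narrower. Its first item is "To increase the hydrocephalus detection rate", followed by shorter time to diagnosis and surgery, better outcomes at discharge, and shorter stay with fewer complications.

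**Reference standard.** None: "Currently, there is no gold standard for its detection" (section 4).

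**Confirmation.** Under section 2.4, a patient with suspected hydrocephalus has a tap test and is assessed 1, 3 and 7 days later. An improvement on any one of the listed scales or functional tests confirms the diagnosis, and a confirmed diagnosis leads to an indication for a shunt.

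**Analyses.** Section 2.5 compares the historical and prospective cohorts on "hydrocephalus diagnosis detection rate, time from admission to diagnosis, LOS, incidence of clinical complications, and DRS and LCF scores at discharge (T3"), with CRS-R in the low-responsiveness subgroup. Within the prospective cohort it compares diagnosed and undiagnosed patients on DRS, LCF and CRS-R at T3 and T4, on quality of life from T0 to T4, and on imaging at T1 and T3 or T4.

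**T2.** Section 2.4 repeats all clinical and functional scales and the CT at T2, which falls "1 month after surgery for those treated with a VPS/VAS or at 3 months from hospital admission" for the patients without a shunt. Section 2.5 does not name T2.

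**The concern.** Detection rate counts how many patients receive the label, and time to diagnosis records when they receive it. Neither shows whether the label is right. Section 3 treats a higher proportion diagnosed as the favourable result, so a protocol that labels more patients scores better whether the extra labels are true or false.

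This matters because a confirmed diagnosis leads towards surgery, and because section 5 foresees adoption by other centres and a contribution to guidelines if the protocol proves useful. A reader told that the protocol was validated would take a higher detection rate as evidence of correct diagnosis. The one later observation that bears on correctness, the change from before to after the shunt, is collected at T2 but has no stated analysis.

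**Working it through.** **1. The article's own figures (section 2.2).** Two years at 50–60 patients a year gives 2 × 50 = 100 to 2 × 60 = 120 patients. At about 20% with hydrocephalus, that is 20 to 24 cases. The stated 100–120 patients and at least 20 cases are reproduced.

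**2. Over-diagnosis needed to reach 20%.** Let p be true prevalence, Se sensitivity and f the false-positive rate among patients without hydrocephalus. Then:

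- detected proportion = p·Se + (1 − p)·f
- PPV = p·Se / detected proportion

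Take p = 0.132, the incidence among 621 patients in the previous study cited in section 1, and Se = 1. Both are assumptions; the article does not give the control cohort's rate.

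- f = (0.20 − 0.132) / (1 − 0.132) = 0.068 / 0.868 = 7.8%
- PPV = 0.132 / 0.20 = 66%
- false positives = 0.068 × 100 = 6.8 to 0.068 × 120 = 8.2, so about 7–8 patients

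**3. The same 20% under other assumptions.**

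| True prevalence | Sensitivity | f needed for 20% | PPV |
|---|---|---|---|
| 13.2% | 0.9 | (0.20 − 0.1188)/0.868 = 9.4% | 59% |
| 13.2% | 1 | 7.8% | 66% |
| 15% | 1 | 0.05/0.85 = 5.9% | 75% |
| 17% | 1 | 0.03/0.83 = 3.6% | 85% |
| 20% | 1 | 0 | 100% |

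The detection rate is identical in every row, so it cannot show which row applies.

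**4. Could over-diagnosis alone give a significant result?** The historical cohort's size is not stated. At the same flow, five years would give 250–300 patients (assumption); 621 is used as an upper value. Power = Φ((d − 1.96·SE₀)/SE₁), with d the difference in proportions, SE₀ pooled and SE₁ unpooled, two-sided 0.05. Prevalence is held at 13.2% and sensitivity at 1:

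| f | Detected | PPV | 250 vs 100 | 300 vs 120 | 621 vs 120 |
|---|---|---|---|---|---|
| 5% | 17.5% | 75% | 0.19 | 0.22 | 0.26 |
| 7.8% | 20.0% | 66% | 0.37 | 0.42 | 0.49 |
| 10% | 21.9% | 60% | 0.52 | 0.59 | 0.67 |
| 15% | 26.2% | 50% | 0.81 | 0.87 | 0.92 |

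Example, f = 15%, 250 vs 100: d = 0.130, SE₀ = 0.0444, SE₁ = 0.0489; (0.130 − 0.087)/0.0489 = 0.88, and Φ(0.88) = 0.81.

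**5. Do the other outcomes check the diagnosis?**

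- Length of stay, complications and discharge scores compare cohorts. They measure the course of recovery, not whether a given patient had hydrocephalus.
- T3 and T4 scores in diagnosed versus undiagnosed patients include post-shunt status, but not the change from before to after the shunt in those operated on.
- Section 3 expects outcomes in diagnosed patients to be similar to those in undiagnosed patients. Labelling unaffected patients as cases would make that easier to meet.

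**The case against.** **Other outcomes are analysed.** A reader might infer that the study looks only at how many are diagnosed. Section 2.5 does not support that: it also compares time to diagnosis, length of stay, complications and discharge scores, with adjustment for confounders. Nor is post-shunt status absent, since T3 and T4 scores enter the within-cohort comparison. The quality-of-life analysis from T0 to T4 might also draw on T2. This stands, and it limits the point to the diagnostic claim.

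**Over-diagnosis need not make the whole study succeed.** Detection is one of four listed aims, and section 5 makes adoption conditional on usefulness. This also stands: only success on the first aim is insensitive to false labels.

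**The tap test is a filter.** Confirmation requires improvement after the test, and the multidisciplinary team reviews the patient. This makes false positives less likely than bare labelling would. But the test is part of the protocol under evaluation, so it cannot serve as its independent check, and one improvement among several measures is enough in patients who are recovering in rehabilitation anyway.

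**The article condenses a fuller plan.** T2 analyses may exist elsewhere. That softens the T2 point. It does not remove the mismatch, which lies between the article's own claim and the comparisons and time points it lists.

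**Shunt response is not a reference standard.** A reader might infer that analysing T2 would establish accuracy. It would not: uncontrolled improvement includes natural recovery, and it says nothing about missed cases.

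**Conclusion.** The concern holds for the diagnostic claim. Validation and accuracy are asserted, no listed analysis measures whether a diagnosis is correct, and the detection rate gives the same result whether the extra cases are true or false.

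The expected rise to 20% could arise with no added true case at a false-positive rate of about 7.8%, with a PPV of about 66%. This assumes a true prevalence of 13.2% and a sensitivity of 1. With sensitivity held at 1 and true prevalence anywhere from 13.2% to 20%, the same detection rate is compatible with a PPV from 66% to 100%. These figures show what the endpoint cannot distinguish; they do not predict over-diagnosis. The 13.2% belongs to a previous study, and the article does not present it as the 2015–2019 control rate.

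The documents do not support the stronger conclusion that the study would succeed overall through over-diagnosis. This is a mismatch between claim and endpoint that should be corrected, at low cost.

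**What to change.** 1. **Restate the aim.** In the Abstract and sections 4 and 5, describe the diagnostic aim and conclusions as increased detection and earlier diagnosis. Do not claim accuracy or validation on the strength of the detection rate. This costs wording only and agrees with the aims listed in section 1.

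2. **Add a supporting descriptive analysis in section 2.5.** Report the proportion of shunted patients whose DRS (with LCF or CRS-R, as section 2.4 uses them) improves from the last pre-operative score to T2, with a 95% CI. Do the same for the historical cohort where the records allow, and interpret the detection rate alongside it. The prospective T2 visit is already scheduled, so the cost is a definition and a small analysis.

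**Limits to state with it:**

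- At most about 20–24 shunted patients are expected, possibly fewer, because section 2.4 says that severity or refused consent can preclude surgery.
- The interval will be wide. At a 50% response the approximate half-width is 1.96 × √(0.25/20) = 22 percentage points with 20 patients, and 1.96 × √(0.25/24) = 20 points with 24.
- Natural recovery counts as response.
- Section 4 warns that historical data may be incomplete, so the comparison between cohorts may be partial.
- The result bears on positive predictive value only, not on missed cases, and so cannot carry the words accuracy or validation either.

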## 5. Conclusions

We designed a novel clinical diagnostic protocol to improve the accuracy of secondary hydrocephalus diagnosis in patients with sABIs. We expect that it will result in a more appropriate assessment and timely treatment of patients, with the ultimate goal of improving their prognosis.

Should this clinical diagnostic protocol prove to be useful, it could be adopted by other rehabilitation centers to improve hydrocephalus diagnosis and treatment, thereby reducing the length of hospital stay and accelerating recovery with benefits for both patients and hospitals. 

In addition, this protocol may inform future diagnostic and prognostic guidelines for the inclusion of the tap test, timely and standardized neuroimaging and an early approach of the multidisciplinary team in the standard of secondary hydrocephalus diagnosis in patients with sABIs. 

## Figures and Tables

**Figure 1 brainsci-13-01067-f001:**
[figure not shown]
Diagnostic protocol timing and procedures.

**Figure 2 brainsci-13-01067-f002:**
[figure not shown]
Study flow-chart.

**Table 1 brainsci-13-01067-t001:** Clinical parameters, scales and exams of the study.

Type of Evaluation	
Clinical parameters	- Neurological status - Presence of tracheostomy or mechanical ventilation - Feeding - Dysphagia - Sensory deficits - Cognitive and behavioral deficits - Clinical complications
Clinical measurement scales	- Glasgow Coma Scale (GCS) [21] - Disability Rating Scale (DRS) [22,23,24] - Levels of Cognitive Functioning (LCF) [24,25,26,27] - Coma Recovery Scale Revised (CRS-R) [28,29,30] - MiniMental State Evaluation (MMSE) [31,32] - Montreal Cognitive Assessment (MoCA) [33] - Modified Ashworth Scale (MAS) [34] - Modified Barthel Index (MBI) [35,36,37] - Glasgow Outcome Scale (GOS) [38] - Quality of Life after Brain Injury Overall Scale (QOLIBRI-OS) [39,40]
Functional tests	- Timed “Up-and-Go” test (TUG) [41] - 10 m Walking Test (10 mWT) [42] - Tinetti Performance Oriented Mobility Assessment (POMA) [43]
Neurophysiological exams	- Electroencephalograph EEG - Event-related brain potential (p300/ERB) - Somatosensory-evoked potentials to upper limb (SEPs)
Neuroradiological exams	- Brain CT scan - Brain 3T MRI

